#### Other outcomes

##### Parental feedback, clinical and spoken language information

A structured parent-report questionnaire will be offered post-intervention, developed from the pilot study [30] to explore enjoyment of the app, engagement with other iPad or computer games, other therapies and to report languages used at home in addition to English (if any).

### Procedure

Participant eligibility will be assessed by the clinical lead, and staff under her direction. Research assistants will ascertain consent, allocate participants according to an independent randomisation procedure (https://SealedEnvelope.com/), and administer assessments, including recording a 12-min video of child and parent in free play for later scoring with the DCMA and BOSCC. The Principal Investigator (PI) received formal training in DMCA and BOSCC coding, which he passed on to the research assistants. The research assistants are trained to a high standard in psychometric and qualitative administration and coding, and receive regular supervision from the PI, the clinical lead, and qualitative specialist. Members of the research team responsible for data collection have completed CPFT Good Clinical Practice training. Parents will receive training to deliver the intervention and will be asked to keep a diary. Parents will be asked to complete the optional think-aloud session and focus group.

### Data management

Data will be anonymised and stored on a restricted shared drive in the CPFT network, to which only the research team will have access. Per the informed consent, anonymised data will be retained permanently (except in the case of withdrawal during the study) and may be released to other researchers. Identifying data (e.g. video, voice) will be deleted after scoring or transcription. Data entry will be completed and checked by research staff. Video data (for DCMA and BOSCC) and voice recordings (think-aloud, focus group, clinician interviews, and diaries) will be stored on a password-protected laptop computer at Nottingham Trent University. Physical data will be stored in locked cabinets within CPFT, accessible only by the research team. Internal data from Point OutWords will be pseudonymised and stored on a file server. The trial statistician and research team will undertake statistical analysis of the data. Only the clinical staff will have access to clinical records. As a small-scale feasibility study, this protocol does not include a data monitoring committee.

### Statistical analysis plan

Results will be analysed by the intention-to-treat principle. Guidelines and standard practices for each outcome measure will be used to impute values for missing items in individual datasets. For example, guidelines for the SRS-2 recommend using the median of the items answered. Any systematically missing subscales within feasibility candidate measures will inform the decision as to which measures would be carried forward to a full-scale RCT. This feasibility trial aims to determine the sample size for the full RCT. Test-retest variances in internal iPad data and external outcome measures will be entered into a standard calculation of statistical power to inform the sample size of a full RCT. Participant flow in terms of recruitment and retention, reported in line with the Consolidated Standards of Reporting Trials (CONSORT) statement for non-pharmacological interventions, will also inform the sample size for a large RCT. The trial statistician will perform the power and sample size calculations. Statistical analysis will be conducted in R.

We will explore the predictability of treatment effects based on the baseline measures. Findings may shed light on whether the intervention is more suited to certain profiles of autism than others. Inclusion criteria for a subsequent full trial would be fixed accordingly. Standardised scores from psychometric assessments will be analysed using mixed-model analysis of variance with time point (pre-intervention, post-intervention) as the within-subjects factor, and treatment (intervention, control) as the between-subjects factor. The internally logged outcome measures of visuomotor accuracy in Point OutWords will be analysed using three separate exploratory analyses of covariance, with Point OutWords usage time, number of distinct Point OutWords sessions, and real time as covariates. Participants’ own responses will be discriminated from caregivers’ model inputs by a statistical clustering method. Fidelity will be assayed using descriptive reports of content, and duration and number of intervention sessions completed.

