## Discussion

Point OutWords was developed in collaboration with children with autism and their therapists and caregivers [30], to include engaging jigsaws, high-contrast graphics, and exogenous cues to help capture and maintain attention, and customisable reinforcement prompts. The interface was adapted to accommodate open-loop visuomotor control (a visuomotor impairment common in people with autism), eliminating a major source of users’ frustration. Working from autistic cognitive strengths, Point OutWords aims to enhance motor skills and to promote representation of objects as sequences (of iconic puzzle pieces, symbolic letters, or symbolic sounds), prerequisite abilities that can support communicative development.

There is a need for therapies that address underserved subpopulations of autism and can be delivered with ease at a low cost. For children with autism who have motor impairment and greater receptive than expressive communication, our new intervention could fill this gap in services were it shown effective in a full-scale RCT. Before such a large-scale study can be framed, a feasibility trial is a necessary step to evaluate recruitment and retention rates and identify actions for reducing attrition. Feasibility trials are especially helpful if the proposed population, in this case, autism with motor impairment, has not previously been specifically tested [65]. Attrition poses a particular challenge with respect to the control group, but we hope that explaining the study’s contribution to science, regularly telephoning families to offer support, and offering the prospect of using Point OutWords after participation in the trial will motivate families to complete the study. As the acceptability of the control apps is a likely predictive factor in reducing attrition in the control group, with advice from parents of autistic children we have selected iPad apps that are enjoyable and fun for children and families. These control apps were selected based on the absence of Point OutWords skills and tasks, as the inadvertent involvement in similar therapy or training in a control group can confound results as recently reported in one large-scale trial [12].

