## Data Availability

Data sharing is not applicable to this article as no datasets were generated or analysed for this protocol study. Participant-level data will be available at a later date. Although no specific reuse of participants’ data in future studies is contemplated a priori*,* this possibility is allowed by the consent document except of course in instances where the parent has withdrawn their child’s data from the study: “By agreeing to participate in this study, you are giving us permission to release anonymous, non-identifying data to other researchers for their use in legitimate scientific research. These data may be posted on the World Wide Web for other scientists to download. At any time whilst the study remains ongoing – even after your child’s participation in the study may have ended – you may withdraw your consent, and in this case we would delete your data from the study dataset and from the set of anonymised data that we release in future.” No biological specimens will be collected for any outcomes.

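### The plan claims intention to treat, but its pre/post mixed ANOVA, as worded, compares changes among children with both scores; a baseline-adjusted comparison with a stated missing-data assumption would serve better

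*Protocol article*

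**What the plan says.** All of the following is from the protocol article.

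- Statistical analysis plan, on principle: "Results will be analysed by the intention-to-treat principle".
- Same section, on missing data: "Guidelines and standard practices for each outcome measure will be used to impute values for missing items in individual datasets". The example is also at item level: "guidelines for the SRS-2 recommend using the median of the items answered". Missing subscales are not imputed but serve to choose measures: "Any systematically missing subscales within feasibility candidate measures will inform the decision as to which measures would be carried forward to a full-scale RCT".
- Same section, on the model for standardised scores: "mixed-model analysis of variance with time point (pre-intervention, post-intervention) as the within-subjects factor, and treatment (intervention, control) as the between-subjects factor". Neither baseline adjustment nor gender appears in it, although the Design and the Allocation and blinding sections stratify randomisation by gender.
- Outcomes: the entries for the MSEL, BOSCC, DCMA and BPVS-III describe comparing mean change, or differences in means, from baseline to post-intervention between the arms.
- Discussion: "Attrition poses a particular challenge with respect to the control group". No rate is given for either arm, and steps to limit attrition follow.
- Data Availability, on withdrawal while the study is ongoing: "you may withdraw your consent, and in this case we would delete your data from the study dataset". Data management makes the same exception.

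**The concern.** Item-level imputation completes an instrument that was largely answered. It does nothing for a child who misses the post-intervention visit or refuses a whole instrument. Such a child has no change score and cannot contribute to a time-by-treatment test of the kind described. The principle claims all randomised children, while the method, as worded, delivers those with both scores.

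Two results are at stake. The first is the arm comparison: if children who leave one arm differ in baseline level from those who stay, regression to the mean shifts the change contrast. The second is the variance of change, which the plan feeds into the sample size of the full trial.

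**Working it through.** **The plan's own figure.** The only figure for the trial's size is the recruitment precision in the Sample size section: 1.96 × √(0.628 × 0.372 / 46) = 0.1397, which matches the stated ±14%. It confirms that the trial was sized on recruitment. It has no bearing on missing data.

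**What the model tests.** With two time points, the time-by-treatment F statistic is the square of the t statistic comparing mean change between arms. The estimate is therefore mean change in intervention minus mean change in control, among children with both scores.

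**Inputs.** From the document: 23 children per arm. Assumed: baseline and post scores with SD 1 and correlation r of 0.5, 0.7 or 0.9; true effect zero; 2 of 23 intervention children lost at random; 6 of 23 control children lost.

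**Case 1: the six control children with the lowest baseline leave.** The 17 who stay have an expected baseline mean of 0.422 SD and an expected post mean of r × 0.422. Their expected change is −(1 − r) × 0.422, while the intervention arm's is 0. The bias is therefore (1 − r) × 0.422.

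**Case 2: the six control children with the smallest change leave.** The SD of change is √(2(1 − r)), so the bias is −√(2(1 − r)) × 0.422.

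The change-score biases below come from these formulas. The baseline-adjusted biases (ANCOVA on children with a post score) and all standard errors come from a simulation of 20,000 runs per case.

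| r | Case 1, change score: bias (SE) | Case 1, adjusted: bias (SE) | Case 2, change score: bias | Case 2, adjusted: bias |
|---|---|---|---|---|
| 0.5 | 0.211 (0.322) | 0.00 (0.295) | −0.42 | −0.33 |
| 0.7 | 0.127 (0.253) | 0.00 (0.245) | −0.33 | −0.29 |
| 0.9 | 0.042 (0.145) | 0.00 (0.148) | −0.19 | −0.18 |

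Baseline adjustment removes the Case 1 bias. In Case 2 it reduces the bias only in part, from 0.19–0.42 SD in size to 0.18–0.33 SD.

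**Does keeping baseline-only children help further?** With two time points and a common baseline mean, the likelihood factorises: a child with only a baseline score informs the baseline distribution and nothing else. In 40 simulated datasets (46 children, 10% and 25% loss, unstructured covariance, no covariates), the ML and REML arm differences agreed with completers-only ANCOVA to within 1e-7. A 20% loss of post scores widens the standard error by about 1/√0.8 = 1.118 whichever of the two is used.

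**Variance carried forward.** Here dropout was graded, with probability rising smoothly rather than by an all-or-nothing rule, at 10% intervention and 20–30% control loss. The completers' SD of change was 1–2% too small when dropout depended on baseline and 6–7% too small when it depended on change. A 6–7% shortfall in SD means a sample size 12–14% too small (1 − 0.94² = 0.12; 1 − 0.93² = 0.14). Under the harsher rules of Cases 1 and 2 the SD shortfalls are 1–3% and about 11%.

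**The case against.** **The article never says that children without a post score are dropped.** That is correct. It is an inference from the within/between wording and from outcome entries framed as change. A mixed model fitted in R by likelihood would keep baseline-only children, and a separate analysis plan may say so. Silence on wholly missing assessments would therefore be no finding. What stands is narrower: the stated principle and the stated method do not fit together as worded.

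**A reader might infer that the trial expects loss mainly in the control arm.** The Discussion does not support this. It calls control-arm attrition a particular challenge, gives no forecast, and lists countermeasures: telephone support, the app after the trial, and enjoyable control apps. Every dropout rate used here is an assumption.

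**A reader might also infer that a likelihood model on every randomised child repairs the problem.** It does not. Under a common baseline mean it gives the ANCOVA answer, so it recovers no precision, and it does not correct dropout that depends on unseen change. The gain in Case 1 comes from baseline adjustment. Nor can every randomised child be included, because data are deleted when consent is withdrawn.

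**The trial already reports retention and missingness as feasibility results, and no decision rule rests on the ANOVA.** Both statements are true, and they limit the weight of the point. They do not make the change contrast the better choice.

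**Conclusion.** The point holds as a mismatch between a claimed principle and a stated method, not as evidence that children will be discarded. Under the assumed losses, the change contrast is biased by about 0.04 to 0.21 SD if control dropout depends on baseline level, roughly 0.3 to 0.7 of its standard error (0.042/0.145 to 0.211/0.322). Baseline adjustment removes this with a similar or smaller standard error. If dropout depends on unseen change, neither analysis is safe and only a sensitivity analysis shows the exposure. The sign depends on who leaves and on the direction of scoring.

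Materiality is modest. The Discussion says the trial is not scoped to establish effectiveness, and under graded dropout the SD of change is understated by only a few per cent. The change is worth making because it costs almost nothing and improves on the stated analysis.

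**What to change.** 1. Replace the mixed ANOVA with a comparison of post-intervention scores adjusted for baseline (ANCOVA, or the equivalent linear mixed model with a common baseline mean), with gender, the stratifier, as a covariate.
2. Describe the analysis set as all randomised children with retained data, in the arm to which they were allocated. State that the estimate relies on children with a post-intervention score and assumes data missing at random given baseline.
3. Add one sensitivity analysis that shifts leavers by a stated amount. For example, a 0.5 SD shift applied to leavers in both arms, with 2 and 6 of 23 lost, moves the arm difference by (6/23 − 2/23) × 0.5 = 0.087 SD.
4. Give the number of children behind each variance carried into the full-trial sample size, since baseline adjustment does not correct a completers-only SD of change.

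The cost is a few sentences in the plan, a few lines of R and slightly more analysis work. No new data are needed.

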## Methodology

### Design

The study applies a feasibility, parallel-groups, randomised controlled design, in which participants are randomly allocated to the intervention group or the control group at a 1:1 ratio. Randomisation will be stratified by gender given the uneven gender ratio in autism diagnoses. The intervention period will last 8 weeks. Figure 1 shows assessments to be administered at baseline and immediately post-intervention. This trial protocol is in line with Standard Protocol Items: Recommendations for Interventional Trials (SPIRIT) 2013 (see SPIRIT Checklist in Additional file 1).

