#### Inclusion criteria

The inclusion criteria are:
Ages 3–15 years.Autism diagnosis confirmed by multidisciplinary assessment as part of routine NHS clinical care, and meeting criteria for autism on the Autism Diagnostic Observation Schedule-Generic (ADOS-G) [32].Nonverbal or minimally verbal (lacking communicative speech or speaking fewer than 100 single words and no phrase speech).Clinical judgement of motor impairment.Clinical judgement that age-adjusted receptive language surpasses age-adjusted expressive language.English is the primary language spoken in the home (as Point OutWords is not yet translated).

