### Allocation and blinding

Individuals will be randomly allocated to the intervention or control group. Participants will be block-randomised, stratified by gender, by the web-based randomisation service Sealed Envelope™ [33], overseen by a trial statistician uninvolved in data collection. Upon obtaining written consent, a research assistant will access Sealed Envelope™ to obtain the treatment allocation, and will therefore be aware of each participant’s allocation, but will be blind to the time point of psychometric assessments at the data analysis stage. Due to the nature of the intervention participants cannot assuredly be blinded to treatment, as they will be aware of the app they are using. The rest of the research team, including the principal investigator and clinical lead, will be blinded to the allocation of each family.

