### Outcomes

#### Primary outcomes

##### Child observations

**Mullen Scales of Early Learning (MSEL)**

The MSEL [43] is widely used as a measure of cognitive ability, motor ability, and language skills in research and clinical evaluations of children with autism [44, 45]. Relevant to the study, the fine motor, receptive language, and expressive language subscales will be administered. Each subscale yields developmental age equivalents, and therefore is applicable to developmentally delayed children outside the 68-month normed age range [46]. The MSEL shows good test-retest and inter-rater reliability [43] and strong concurrent validity with other developmental tests of motor and language, including the Vineland Adaptive Behaviour Scales II (VABS-II) [44]. Differences in mean scores from baseline to post-intervention between the intervention and control group will measure treatment efficacy. Separately, baseline mean scores will be used to characterise for whom the treatment is (or might be) effective. For example, a disparity in age-equivalent scores between the receptive and expressive language domain might predict treatment effects.

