**Brief Observation of Social Communication Change (BOSCC)**

The BOSCC [47] is scored from a 12-min video recording of a parent-child play session, coded on 16 items assessing atypicality, frequency, and severity of autistic symptoms. The BOSCC coding scheme was developed from the Autism Diagnostic Observation Schedule (ADOS)-2 [48] by the same research team, to detect clinically significant changes in autistic symptoms following treatment. The BOSCC has yielded excellent inter-rater reliability and high test-retest reliability [47]. Treatment efficacy will be measured by differences in mean scores from baseline to post-intervention between the intervention and control groups.

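### The time × treatment ANOVA is a change-score comparison that leaves out baseline adjustment and the gender stratum; it is unbiased but less precise than ANCOVA, and the variance passed to the full trial is undefined

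*Protocol article*

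**What the plan says.** The Statistical analysis plan section names two factors and no covariates for the psychometric outcomes: "mixed-model analysis of variance with time point (pre-intervention, post-intervention) as the within-subjects factor, and treatment (intervention, control) as the between-subjects factor". The individual outcome sections describe matching comparisons. For the BOSCC, for example: "Treatment efficacy will be measured by differences in mean scores from baseline to post-intervention between the intervention and control groups".

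Gender is the stratification factor. The Design section says "Randomisation will be stratified by gender given the uneven gender ratio in autism diagnoses", and Allocation and blinding repeats it: "Participants will be block-randomised, stratified by gender". Gender does not appear in the analysis model. Baseline scores enter that model only as one level of the time factor. Their other stated use is exploratory: to see which children might benefit.

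On age, the inclusion criterion is "Ages 3–15 years", and age is not a stratification factor. The analysis section says "Standardised scores from psychometric assessments will be analysed", while for the MSEL the protocol relies on age equivalents for children beyond the normed range: "Each subscale yields developmental age equivalents".

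For the full trial, the plan states: "Test-retest variances in internal iPad data and external outcome measures will be entered into a standard calculation of statistical power". It does not say which variance this is, and it does not state how the full trial would be analysed.

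**The concern.** The model is a stated choice, not a detail left to a later document. A comparison of change scores subtracts the whole baseline value, whatever the baseline–post correlation. ANCOVA subtracts only the part that predicts the post score. The change-score comparison is therefore noisier whenever that correlation is below 1. It also over-corrects a chance baseline difference, through regression to the mean. Leaving out a factor used to stratify randomisation gives up any precision that the stratification bought.

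This matters beyond the 46 children because variance is a main product of a feasibility trial. The protocol says that variance in the outcome measures will inform both the choice of measures and the size of the full RCT. If the variance carried forward does not match the full trial's analysis model, that trial will be wrongly sized.

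**Working it through.** **The plan's own figure.** The only sample-size figure is the precision of the recruitment rate: 1.96 × √(0.628 × 0.372 / 46) = 13.97 percentage points, which agrees with the stated ±14%. It does not depend on the outcome model.

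**The interaction is a change-score test.** In one simulated data set with 23 per arm, the split-plot interaction F was 4.788 and the squared t statistic on change was 4.788.

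**Variance per child.** Set the pre and post SDs equal to 1, with within-arm correlation rho:

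- change score: 2(1 − rho)
- baseline-adjusted ANCOVA: 1 − rho²
- ratio: 2(1 − rho) / [(1 − rho)(1 + rho)] = 2/(1 + rho)

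The document gives no SD, rho, effect size, alpha or power for the outcomes. The table therefore assumes a range of rho and, for illustration, a difference of 0.5 SD, two-sided alpha 0.05 and 80% power.

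| rho (assumed) | Change-score variance | ANCOVA variance | Ratio | n per arm, change | n per arm, ANCOVA |
|---|---|---|---|---|---|
| 0.5 | 1.00 | 0.75 | 1.33 | 63 | 48 |
| 0.7 | 0.60 | 0.51 | 1.18 | 38 | 33 |
| 0.8 | 0.40 | 0.36 | 1.11 | 26 | 23 |
| 0.9 | 0.20 | 0.19 | 1.05 | 13 | 12 |

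The protocol quotes one numerical test-retest reliability, .88 to .90 for the VMPAC subtests. It gives 2/1.88 = 1.06 and 2/1.90 = 1.05, an excess of 5 to 6%.

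**Chance baseline imbalance.** With 23 per arm, the SD of the baseline difference is √(2/23) = 0.295 SD. The chance that it exceeds 0.5 SD in either direction is 2 × [1 − Φ(0.5/0.295)], about 9% per measure. Over the ten psychometric instruments, the expected number is about 10 × 0.09 = 0.9.

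**Gender and age.** A small simulation used 23 per arm and assumed about 20% girls and an age–score correlation of 0.5.

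- In the change-score model at rho 0.8, adding both covariates left the residual variance unchanged when neither predicts change (0.402 against 0.401).
- With assumed effects on change of 0.3 SD for gender and 0.2 SD per SD of age, it fell from 0.457 to 0.401, about 12%.
- In ANCOVA, when neither predicts change, adding both lowered the residual variance from 0.754 to 0.668 at rho 0.5 and from 0.361 to 0.347 at rho 0.8. That gain comes from age being related to the level of the score, as it would be for age equivalents.
- Two covariates that explain nothing cost about 44/42 = 1.05, or 5%. They break even at a partial R² of about 0.05.

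**The case against.** The strongest reply is that little depends on this test. The Discussion says the trial is not scoped to establish whether the intervention works. The sample size rests on recruitment, and no feasibility decision is tied to the time × treatment result. A change-score comparison of randomised groups is unbiased. If the real correlations are near the VMPAC figure, the loss is about 5%. All of this stands, and it makes the point one of efficiency. Correlations over 8 weeks of intervention may be lower than published retest reliability, though, and other instruments may differ.

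A reader might infer more than the document supports:

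- **That the plan overstates the full trial's sample size.** The variance carried forward is undefined and is not tied to the ANOVA residual. If the full trial also compares change, the change-score variance is the right one.
- **That baseline imbalance is likely on several instruments.** At about 9% per measure, roughly one in ten is expected.
- **That the treatment main effect, which averages pre and post scores, would be reported as the treatment effect.** The outcome sections describe between-group comparisons of change or of pre and post scores, and nothing points to the main effect.
- **That omitting age contradicts the design.** Age is not a stratification factor. Differencing removes stable age effects, and age-normed scores are already adjusted. Age has a clear role only for scores that are not normed.
- **That omitting gender biases the result.** It tends to make the test conservative, by an amount that cannot be computed from the document.

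**Conclusion.** The point holds as a modest, low-cost improvement. The specified model is a change-score comparison that neither conditions on baseline nor includes the randomisation stratum. Compared with ANCOVA its variance is larger by 2/(1 + rho): 33% at rho 0.5, falling to about 5% at 0.9. These figures assume equal pre and post variances and assumed correlations, so none of them is a property of this trial. The assured gain comes from baseline adjustment. What gender and age add depends on whether they predict the outcome.

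The consequence for the full trial is conditional. Its size would be inflated by the same factor only if change-score variances are carried forward and that trial uses ANCOVA. What can be said without condition is that the plan does not define the variance or match it to an analysis model.

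**What to change.** For each psychometric outcome, fit a linear model of the post-intervention score on treatment, baseline score and gender. Add age only where the score is not age-normed, as with MSEL age equivalents. Report the adjusted mean difference with its 95% confidence interval.

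Replace the undefined test-retest variances with named quantities: the post-score SD and the within-arm baseline–post correlation, or the ANCOVA residual variance. State the full trial's intended analysis model and use the variance that matches it. Reporting the SD and the correlation allows either calculation later.

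The cost is a paragraph of text. Baseline scores, gender and age are already available. The model uses two of the 44 residual degrees of freedom that the change-score test has with 46 children, and a third where age is added.
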